#### Statistical analysis

Descriptive statistics are used to describe the data included for the statistical analysis and are reported as the mean, standard deviation, median, quartile and ranges as well as absolute and relative frequencies. The primary endpoint is the asthma knowledge gain after the eAEP (two weeks after study inclusion) and fAEP (twelve weeks after study inclusion), respectively. A confirmatory hypothesis test for difference between intervention and control group is performed by a linear mixed-effects model at a two-sided 5% significance level. Based on the intention-to-treat principle, all patients will be included in analysis. The baseline value (number of correctly answered questions in the AKT at baseline), time since eAEP/fAEP, and group allocation (intervention or control group) will be used as fixed effects. Cluster effects of the general practices will be included in analyses as random intercepts. As previously mentioned, missing data for this variable will be imputed by performing a worst-case-analysis. Thereby, the average knowledge gain for drop-out patients is expected to be 0 points in the intervention group and 10 points in the control group. A comparison of the asthma knowledge gain between intervention and control group will also be made three months after completion of the eAEP (three months after study inclusion)/fAEP (six months after study inclusion) and at the end of the study (six-month follow-up). Similar calculations will be applied for the secondary outcome asthma control (difference in the achieved sum score of the ACT three months after completion of the eAEP/fAEP as well as at the six-month follow-up) (see Table 2). Emergency treatments as a secondary outcome will be considered binary in the analyses (0: No; 1: Yes, at least one emergency treatment). Due to the consideration of measurement repetition as well as data grouped in clusters, generalized estimating equations (GEE) will be applied. Group allocation is used as a covariate. Spearman or Pearson correlation coefficients will be calculated for the relation between 1) patients’ autonomy preference and asthma knowledge as well as between 2) patients’ attitude towards asthma medication and asthma knowledge. All analyses will be conducted exploratively with and without imputation in terms of a worst-case-analysis.

**Table 2 Tab2:** Overview of primary and secondary endpoints of the respective outcomes for linear mixed-effects models

			Time point (t)	
Outcomes			Intervention group	Control group
Asthma knowledge	Primary endpoint	AK gain **after** eAEP / fAEP	Two weeks after study inclusion	Twelve weeks after study inclusion
	Secondary endpoints	AK gain **three months** after eAEP / fAEP	Three months after study inclusion	Six months after study inclusion
		AK gain **at the end of the study**	Six months after study inclusion	Six months after study inclusion
Asthma control	Secondary endpoints	Total sum core in the ACT **three months after** eAEP / fAEP	Three months after study inclusion	Six months after study inclusion
		Total sum core in the ACT **at the end of the study**	Six months after study inclusion	Six months after study inclusion

*Annotation:* Planned model for confirmatory hypothesis test for difference between intervention and control group: Linear mixed-effects model (5% significance level). *AK* implies asthma knowledge, *eAEP* electronic asthma education program, *AEP* asthma education program, *ACT* asthma control test

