### Aims and Outcomes

This cluster randomized controlled trial (cRCT) aims to investigate the effectiveness of the eAEP compared to usual care in terms of 1) asthma knowledge, 2) asthma control, and 3) emergency treatments including the following endpoints:Baseline-adjusted difference in the number of correctly answered questions in the AKT [8] between intervention and control groupsprimary endpoint: after the eAEP (two weeks after study inclusion) and fAEP (twelve weeks after study inclusion), respectively.secondary endpoint: three months after the eAEP (three months after study inclusion) and fAEP (six months after study inclusion), respectively.secondary endpoint: at the end of the study (six-month follow-up).

Further secondary endpoints include:2)Baseline-adjusted difference in the total sum score obtained in the asthma control test (ACT) [9] between intervention and control groupsthree months after the eAEP (three months after study inclusion) and fAEP (six months after study inclusion), respectively.at the end of the study (six-month follow-up).3)Difference in frequency of emergency treatments (inpatient and outpatient treatments of asthma) between intervention and control groups at six months.

This trial further examines the relation between asthma knowledge and 4) patient autonomy as well as 5) attitudes towards asthma medication including the following endpoints:4)Correlation between the total sum score achieved in the autonomy preference index (API) [10] at the time point baseline assessment and the change in correctly answered questions in the AKT after the eAEP and fAEP, respectively.5)Correlation between the total sum score obtained in the questionnaire on attitudes towards asthma medication at the time point baseline assessment and the change in correctly answered questions in the AKT after the eAEP and fAEP, respectively.

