### Recruitment and Randomization

In this study, 20 general practices in Bavaria, Germany, will be included. Practices will be recruited by contacting GP’s of the institute’s teaching practices network and of the bavarian practice-based research network (BayFoNet). The Institute of General Practice and Family Medicine, Ludwig-Maximilians-University in Munich (LMU Munich) and the Institute of General Practice, Friedrich-Alexander University Erlangen-Nürnberg (FAU), which are also part of BayFoNet, will support recruitment of general practices. The allocation of the general practices to the intervention or control group will be conducted by a statistician [name] of the study team, whom is not involved in the study conduct. For this purpose, a randomization sequence will be generated using the program R (The R Foundation for Statistical Computing, Vienna, Austria). The allocation ratio of intervention to control group at 1:1, no stratification, and randomly varying block sizes will be documented in advance. The randomization list will be prepared and retained by the statistician. After inclusion of general practices in the study, practices will be consecutively added to the randomization list by the statistician and assigned an appropriate sequential number. The statistician will report the corresponding classification of the practice into the study arm to the study coordinator.

After allocation of the general practice to the intervention or control group, patients will be consecutively recruited by the participating general practice. Patients will not be blinded with regard to the intervention. The practice team will check the inclusion and exclusion criteria. Furthermore, the attending physician will inform patients about the study. If patients may be eligible for the study but are unwilling to participate, age, sex, and the reason for non-participation will be documented anonymously using a non-responder list. Thus, it is possible to conduct a non-responder analysis to assess acceptance of the eAEP offer as well as fAEP.

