### Statistics

#### Sample size estimation

The power calculation is based on the results of the pilot study conducted in 2019 [7] using a two-sample t-test: An average difference of 22 points in the AKT (corresponding scale ranges from 0 to 54 points) was observed between baseline measurement and after completion of the eAEP (two weeks after study inclusion). A more conservative approach of an average difference of 20 points is applied for planning the current study. As the pilot study did not include a control group, an average asthma knowledge gain of 5 points was estimated for the control group of the present study. This estimation is based on the assumption, that about 25% of the patients in the control group will attend a fAEP and therefore achieve an average knowledge gain of maximum 20 points [3, 4]. The remaining 75% of the patients are expected to reach an average knowledge gain of 0 points. This results in 0.25 x 20 points + 0.75 x 0 points = 5 points. In order to include all available data in statistical analyses as well as to prevent an attrition bias, the intention-to-treat principle is applied in this study with an expected drop-out rate of 20%. Performing a worst-case-analysis [15], it is assumed that drop-out patients in the intervention group achieve an average knowledge gain of 0 points. Accordingly, an average asthma knowledge gain of 16 points is expected in the intervention group (0.80 x 20 points + 0.20 x 0 points). Considering a worst-case-analysis, the average asthma knowledge gain is assumed to double for drop-out patients in the control group resulting in an average knowledge gain of 6 points (0.80 x 5 points + 0.20 x 10 points). The sample size estimation is based on a standard deviation of 15. Using a two-sample t-test and a two-sided 5 % significance level, the number of patients per group is 36 to achieve a power of 80 %. Due to cluster randomization, the number of patients has to be increased by the design effect (DE). The sample size estimation of the current study is based on an intracluster correlation coefficient (ICC) of 0.10 [16], a mean cluster size of 5 and a resultant DE of 1.4 (calculation based on [13]). Regarding the primary outcome asthma knowledge gain, the number of patients required is therefore 100 (2 x 36 x 1.4 ≈ 100).

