Nonetheless, a common and well-known disadvantage of cRCTs may be the differences in recruitment between intervention and control groups [21]. In most cases, the allocation to the intervention group might be more attractive leading to an increased recruitment of patients and thereby evoking a risk of selection bias. However, a major advantage of cRCTs is the avoidance of contamination of care. Therefore, it is most reasonable to select this study design as it allows to estimate the impact of the eAEP compared to usual care. Furthermore, it is likely that patients of younger age as well as higher education level are more prone to participate in this study as it involves engagement in an online program and thereby requiring skills and knowledge in internet applications. However, the pilot study in 2019 has shown that patients were comparatively older with a mean age of 48 years. Furthermore, it has been shown that patients had a rather standard education [7]. In the present study, the asthma knowledge of patients of both the intervention as well as control groups will be assessed two weeks after study enrolment. While it is assumed that patients of the intervention group have already completed the eAEP by this time, it is rather unlikely that patients of the control group will be able to attend a fAEP immediately after referral. Nevertheless, we aim to investigate the asthma knowledge gain within the context of clinical reality. Another challenge to face might be the repeated measurement of asthma knowledge using the same questionnaire. Applying the same knowledge test several times could result in an increase in correctly answered questions and thereby in a better performance. Nevertheless, as this questionnaire involves 54 items addressing a great variety of topics, this phenomenon seems rather unlikely to happen. In addition, the fact that the eAEP is only available in German so far, could present a further limitation. It prevents patients incapable of understanding and speaking German from participating in the study. Therefore, the study population may not be representative of the general population and thereby the generalizability of the results may be limited. However, it is assumed that most of the asthma patients visiting general practices are eligible to participate in the study as there are only few exclusion criteria included.

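### The confirmatory model adjusts for no baseline patient characteristic except AKT, although practices recruit patients after allocation; pre-specifying age, sex and baseline API would be a cheap improvement

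*Protocol article*

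**What the plan says.** **Model.** Under Statistical analysis, the primary comparison is a linear mixed-effects model tested at a two-sided 5% level. Baseline AKT is the first fixed effect; the sentence then continues "time since eAEP/fAEP, and group allocation (intervention or control group) will be used as fixed effects". Practice is a random intercept. The secondary AKT and ACT endpoints get similar models.

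**Recruitment.** Recruitment and Randomization describes 1:1 allocation of 20 practices without stratification. Patients are recruited once their practice has been allocated, and they are not blinded. For eligible patients who decline, "age, sex, and the reason for non-participation will be documented anonymously using a non-responder list".

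**Participation.** The Discussion acknowledges that the intervention arm may attract more patients in a cluster trial and that this risks selection bias. It adds that "it is likely that patients of younger age as well as higher education level are more prone to participate in this study" and gives the online programme as the reason. Control patients receive access to that programme only at the end of the study (Control Group).

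**Autonomy preference.** One secondary endpoint is the "Correlation between the total sum score achieved in the autonomy preference index (API) [10] at the time point baseline assessment" with the later change in AKT. The API is completed at baseline in both arms.

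**The concern.** Randomising practices does not by itself make patients comparable when they are enrolled after the practice has been allocated. If the prospect of an online programme draws younger or better-educated patients into intervention practices, the arms can differ systematically. Any part of that difference which predicts knowledge gain, and which baseline AKT does not capture, would enter the confirmatory estimate. The protocol names the selection risk, but in design and primary model only baseline AKT addresses patient-level imbalance. A second, smaller stake is precision: outcome variance that baseline covariates could explain stays in the standard error.

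**Working it through.** **1. The plan's own sample size.** Inputs from Sample size estimation:
- "an average asthma knowledge gain of 16 points is expected in the intervention group".
- In the control group, drop-out patients' gain is assumed to double, "resulting in an average knowledge gain of 6 points (0.80 x 5 points + 0.20 x 10 points"). The difference is 16 − 6 = 10 points.
- SD 15, ICC 0.10, mean cluster size 5.
- "Using a two-sample t-test and a two-sided 5 % significance level", "the number of patients per group is 36 to achieve a power of 80" per cent.

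The normal approximation gives 36 per group. The exact t calculation gives 79.7% power at 36 and 80.8% at 37. The design effect is 1 + (5 − 1) × 0.10 = 1.4, and 2 × 36 × 1.4 = 100.8, which the plan rounds to 100. The figure reproduces. It takes no credit for any covariate, so the planned size does not depend on the adjustment discussed here.

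**2. Starting precision.** With 50 patients per arm (10 practices of 5), SE = 15 × √(2 × 1.4/50) = 3.55 points. Power for a 10-point difference is 80.4% by the normal approximation. With degrees of freedom at practice level (20 − 2 = 18) it is 75.9%. The step from 80.4% to 75.9% comes from the degrees of freedom and has nothing to do with covariates.

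**3. Possible gain in precision.** The documents do not say how much variance age, sex, education or API explain beyond baseline AKT, so R² is an assumption. Using SE × √(1 − R²) on 18 df:

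| Extra R² (assumed) | SE | Power |
|---|---|---|
| 0 | 3.55 | 75.9% |
| 0.02 | 3.51 | 76.8% |
| 0.05 | 3.46 | 78.0% |
| 0.10 | 3.37 | 80.2% |
| 0.15 | 3.27 | 82.4% |

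For R² of 0.02 to 0.10 the gain is about 1 to 4 percentage points. This assumes that the covariates reduce the between-practice and within-practice variance in proportion. If they explain only within-practice variance, the gain is smaller. At R² 0.10 the total variance is 225, with 22.5 between and 202.5 within practices. The SE becomes √(2 × [22.5/10 + (202.5 − 22.5)/50]) = 3.42, and power is 79.0%.

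**4. Possible shift from recruitment imbalance.** For a covariate with correlation r with gain (given baseline AKT) and a standardised difference d between arms, the shift is 15 × r × d. Both r and d are assumptions.

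| r | d | Shift (points) | Rejection rate under no effect |
|---|---|---|---|
| 0.2 | 0.3 | 0.90 | 5.7% |
| 0.3 | 0.3 | 1.35 | 6.5% |
| 0.2 | 0.5 | 1.50 | 6.9% |
| 0.3 | 0.5 | 2.25 | 9.2% |

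The rejection rates use a noncentral t on 18 df and hold d fixed in one direction, so they describe systematic recruitment differences only. Using the full SD of 15 with a correlation conditional on baseline AKT makes the shifts, if anything, too large.

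**5. Chance imbalance for comparison.** The SD of d under chance alone is √(2/50 × [1 + 4 × ICC]), which is 0.20 for a covariate ICC of 0 and 0.24 for an ICC of 0.10. A difference of 0.5 is thus at least a 2-SD event by chance.

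**The case against.** The strongest reply is that nothing here is wrong. The model adjusts for the baseline value of the outcome, normally the most useful covariate, and that will absorb at least part of any influence of age or education on knowledge. Further covariates are a design choice. This stands, and it limits the point to an improvement.

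A reader might infer that the protocol itself identifies age, education and autonomy preference as predictors of knowledge gain and then ignores them. It does not. The remark on age and education concerns who joins the study, and the Discussion tempers it at once with pilot patients who were comparatively old (mean age 48) and of rather standard education. The API relation is a correlation to be examined. A participation driver biases the comparison only if it acts differently by arm and also predicts gain given baseline AKT; the protocol asserts neither. What remains is that the stated reason for selective participation is a programme only the intervention arm receives during the study, so an arm-specific effect is plausible.

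A reader might also infer that chance imbalance biases the primary result. Averaged over randomisations it does not, and the standard error already covers it.

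Two further limits stand. Adjustment cannot remove differences in unmeasured traits such as motivation or internet skill. The article also does not show that education is recorded, and that participants' age and sex are available is an inference from the possible non-responder analysis.

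**Conclusion.** The point holds as a modest, nearly costless improvement to a covariate list that the article states explicitly. With recruitment after unstratified allocation and a conceded selection risk, a confirmatory model with baseline AKT as its only baseline patient covariate leaves available protection unused. It remains a valid model under unbiased recruitment.

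The benefit is about 1 to 4 points of power for an assumed extra R² of 0.02 to 0.10 on 18 df, plus partial removal of any measured recruitment imbalance. An illustrative shift is 0.9 points (r = 0.2, d = 0.3), about a quarter of the standard error and 9% of the planned difference. The 9.2% rejection rate needs the largest assumed correlation and the largest assumed imbalance together, and should not be read as the expected error rate of the trial.

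**What to change.** In the analysis plan, before outcome data are seen, add age, sex and baseline API as patient-level fixed effects to the primary AKT model and to the secondary AKT and ACT models. Add education level only if the baseline form records it. Keep the practice random intercept. Report the model with baseline AKT as the only baseline patient covariate as a sensitivity analysis, and state how occasional missing covariate values are handled.

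The cost is a few lines of text, three or four patient-level degrees of freedom out of 100 patients, and a simple rule for missing covariates. In a linear model, adjusting for these baseline values leaves the treatment contrast being estimated unchanged. The sample size need not be revisited for this point.

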#### Patient questionnaire two weeks after study inclusion (t_*1*_)

All patients will receive a questionnaire by mail two weeks after study inclusion. Patients in the intervention group will be asked to complete the AKT again after they have completed the eAEP. Patients in the control group will also receive the AKT after two weeks, even if no fAEP has been attended by this time. Thus, it will be assessed whether they have already acquired knowledge about the disease independently of a fAEP using other sources such as the internet. In addition, patients from general practice in the intervention group will be asked about their internet use in general and whether they had participated in a fAEP in addition to completing the eAEP.

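### The confirmatory test imputes missing AKT gains as 0 (eAEP) and 10 (control), so it does not keep its two-sided 5% level and distorts the estimate, mainly against the eAEP

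*Protocol article*

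**What the plan says.** The Statistical analysis section says that the comparison of AKT gain between the arms "is performed by a linear mixed-effects model at a two-sided 5% significance level", with all patients included by intention to treat. In the same description it says that "missing data for this variable will be imputed by performing a worst-case-analysis" and gives the values: "the average knowledge gain for drop-out patients is expected to be 0 points in the intervention group and 10 points in the control group". The section ends by planning all analyses with and without this imputation, but calls them exploratory. The natural reading is that the confirmatory result contains the imputed values.

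The Sample size estimation section uses the same rule. Intervention drop-outs are given a gain of 0, and "the average asthma knowledge gain is assumed to double for drop-out patients in the control group", that is from 5 to 10. With 20% drop-out the planning means of 20 and 5 become 16 and 6.

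The section on the two-week questionnaire mails the AKT to all patients and adds: "Patients in the intervention group will be asked to complete the AKT again after they have completed the eAEP".

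**The concern.** A test of no difference should be centred on zero when the arms do not differ. Here every drop-out adds a difference fixed in advance by arm, so the contrast is off zero under the null and the rejection rate is no longer 5%. The imputed values also have no spread, so they reduce the observed variance and the standard error treats them as measured gains. At stake are the trial's headline estimate, its interval and the meaning of its p-value: all three would mix measured knowledge gains with assumed ones, in a proportion set by the drop-out rate.

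**Working it through.** **Inputs.** All are from Sample size estimation unless noted.
- Gains of 20 ("A more conservative approach of an average difference of 20 points is applied for planning the current study") and 5 (0.25 x 20 + 0.75 x 0)
- SD 15 ("The sample size estimation is based on a standard deviation of 15")
- Drop-out 20%, not split by arm
- ICC 0.10, mean cluster size 5, 100 patients
- Imputed values 0 and 10 (Statistical analysis)
- 20 practices allocated 1:1 (Recruitment and Randomization)

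**The plan's own figure.** For a difference of 16 - 6 = 10 and SD 15, a two-sample t-test at 5% and 80% power needs 36.3 per group. This agrees, up to rounding, with "the number of patients per group is 36 to achieve a power of 80" per cent. The design effect is 1 + (5 - 1) x 0.10 = 1.4, and 2 x 36 x 1.4 = 100.8, stated as about 100. The calculation reproduces, with the penalty included.

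**Bias.** Let the true gains be mI and mC with difference delta = mI - mC, and let drop-out be d in both arms and unrelated to outcome.

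Imputed contrast = (1 - d) x mI - [(1 - d) x mC + 10d] = (1 - d) x delta - 10d.

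Bias = -d x (10 + delta).

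- Null (delta = 0), d = 20%: -0.20 x 10 = -2 points. At d = 40%: -4 points.
- Planning values (delta = 15), d = 20%: -0.20 x 25 = -5 points, so 15 becomes 10, one third smaller.

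**Level of the test.** Simulation of 10 practices per arm with 5 patients each, SD 15, ICC 0.10, a common gain of 5, constants imputed, and a t-test on practice means (18 df) standing in for the mixed model:

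| Drop-out, both arms | Two-sided error |
|---|---|
| 0% | about 5% |
| 10% | about 6% |
| 20% | about 10% |
| 30% | about 18% |
| 40% | about 32% |

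At 20%, about 9.5 percentage points run against the eAEP and about 0.4 to 0.5 in its favour. The same test on observed data only stays at about 5%. If the stated averages are read as centres of a distribution with SD 15 instead of constants, the error at 20% is still 9.0%.

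**Power.** At 20 versus 5 with 20% drop-out, simulated power is about 83% with the imputation and about 95% on observed data, if data are missing at random.

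**Is 10 a worst case?** It is twice an assumed control mean of 5. The same section allows fAEP attendees up to 20 points, so the control mean would pass 10 if more than half attended (0.50 x 20 = 10). With a common true gain g and drop-out dI and dC, the bias under the null is

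g x (dC - dI) - 10 x dC.

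This is positive only if g exceeds 10 and control drop-out is sufficiently higher. For illustration (assumed, not from the protocol), g = 20 with drop-out of 5% (eAEP) and 40% (control) gives 20 x 0.35 - 4 = +3 points and about 15% false eAEP superiority. With 10% and 30% it gives 20 x 0.20 - 3 = +1 point and about 5%. With equal drop-out it stays at -10d whatever g is.

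**The case against.** The strongest defence is that the rule is deliberate, prespecified and conservative. The sample size budgets for it, the planned power is met, and at equal drop-out a false claim for the eAEP falls from 2.5% to about 0.4 to 0.5%. A run without imputation is planned as well. All of this is correct. It does not rescue the estimate or the stated level: the test is two-sided and can wrongly declare the online programme inferior, and the run without imputation is only exploratory.

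A second argument concerns the repair. Intervention patients are asked for the AKT after finishing the eAEP, so non-finishers may be the ones missing. Their true gain may be near 0, in which case imputing 0 is sensible for them and a missing-at-random model would flatter the eAEP. This stands as a caution. It is an inference, since the questionnaire is mailed to everyone, but it is why the 0/10 analysis should be kept and not deleted.

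A reader might go further and infer three things that the document does not support:
- **The trial is underpowered or its sample size wrong.** The penalty is already in the 16 versus 6.
- **The rule inflates false claims for the eAEP.** On the plan's figures it does the reverse.
- **The imputation is simply not worst-case.** That needs gains above 10 and clearly higher control drop-out, whereas the plan assumes 25% fAEP attendance and a control mean of 5.

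**Conclusion.** The point holds in this form: the confirmatory test as written does not have a two-sided 5% level, and its estimate is displaced by the imputation rule. At the planned 20% drop-out the error is about 10%, nearly all against the eAEP. The displacement is -2 points under the null and -5 points at the planning values. A bias of -10 times the drop-out rate is not a general result; it applies only when the arms truly do not differ and drop out equally.

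The figures assume drop-out unrelated to outcome, normally distributed gains, no baseline covariate and a practice-mean t-test in place of the mixed model. A smaller residual SD, as baseline adjustment might give, makes the level worse: at 20% drop-out the error is 15.7% for an assumed SD of 10 and 21.3% for an assumed SD of 8. The reversal in favour of the eAEP is a conditional risk, not an expectation. The change should be made, although the fault as planned is mostly conservative.

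**What to change.** 1. Make the confirmatory analysis a likelihood-based linear mixed model on the observed AKT scores with practice and patient random effects, or multilevel multiple imputation by arm using t0 to t3. State explicitly that the tested contrast is the protocol's own: week 2 in the eAEP arm against week 12 in the control arm.
2. Keep the 0/10 imputation as a prespecified sensitivity analysis, within a delta or tipping-point range that includes a gain near 0 for eAEP non-finishers and values above 10 for controls.
3. Ask intervention patients to return the t1 AKT whether or not they have finished the eAEP.

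The cost is statistical wording and one sentence in the t1 mailing; no new assessment is needed and the sample size can stay. The downside is that the primary analysis then rests on missing at random, which the retained sensitivity analysis is there to probe.
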